### Statistics

The data analysis will be performed at the end of intervention including the measurement values from pre- and post-intervention measurements. Data will be tested for normal distribution using Shapiro-Wilk test and Q-Q-plots. A 2 × 2-ANOVA will be used with normally distributed data, the non-parametric equivalent for data not fulfilling assumptions of normal distribution. The test will be used to compare the two interventions over time (from pre- to post-measurement) on changes on the main dependent variables MEP, RRP, RT of cognitive tasks, spatio-temporal gait parameters, DTC, and FA levels. In addition to statistical significance testing effect size calculation (*r* = Z/√N) will be performed. The participants' FA blood levels, demographic, and health information will be examined in relation to the outcome measures in order to interpret the results in context. All statistical procedures will be conducted with the IBM Statistical Package for the Social Science software package. A probability level of *p* < 0.05 will be considered to be statistically significant.

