A systematic review revealed that previous interventions using a combined approach of PE and NS to effect on the brain were not particularly successful because of the misfit between the combinations; the intervention components were not selected based on sharing of similar neuronal mechanisms (Schättin et al., 2016). The review indicates, however, that especially fish oil, containing omega-3 fatty acid (FA), might be an effective NS supporting the positive effects of PE. Omega-3 FA is important for energy metabolism and for the composition of the plasma membranes in the brain (Gómez-Pinilla, 2008). Another review showed that long chain polyunsaturated FA (LCPUFA) might improve cognition, decrease (neuro) inflammation, and reduce vascular risk factors in normal aging adults (Janssen and Kiliaan, 2014). Omega-3 LCPUFA may provide decreased brain deterioration through the positive effects on brain structure, function, and cerebral blood flow (Haast and Kiliaan, 2015). A recent randomized-controlled study showed that fish oil had positive effects on brain structure and function in healthy older adults (Witte et al., 2014). The participants showed improved EFs, white matter microstructure integrity, gray matter volume, and vascular parameters.

So far no study investigated the combined effect of exergame training and omega-3 FA on the elderly brain's structure and function. This study, therefore, aims to investigate the effects of a combination of exergame training and omega-3 FA. The following research question will guide through the research process: “Does the combination of exergame training and fish oil differently affect neuronal system levels in the elderly brain compared to exergame training alone?” The main objectives of the trial are (1) to determine the effects of the intervention on the neuronal structural level of the brain (neuronal excitability) and (2) to assess the effects on functional level in the brain (neuronal activity). We hypothesize that the combination will differently affect these parameters.

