### Sample size

To avoid a type I or II error, the power calculation was based on a study examining the effect of omega-3 FA on EEG frequency band distribution during a sustained attention test (Fontani et al., 2005). The aforementioned study was used for sample size calculation because so far there exists no study that examined the influence of exergame training in combination with omega-3 FA on neuronal systems using TMS or EEG methodology. Due to the values of EEG frequency band distribution during sustained attention tests (with values K + K = 27.70 ± 5.2; K + K = 31.49 ± 8.6), an estimated sample size of 24 participants would result in 80% power at an alpha-level of 0.05 for this parameter. To account and compensate for expected drop-outs, the study includes 30 participants in each group. Drop-outs are expected because of the long study duration of 26 weeks, the age of the participants, and numbers are based on previous reports on adherence of non-institutionalized older adults to exercise programs (Nyman and Victor, 2012).

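### The planned 2 × 2 ANOVA is in effect a change-score t-test, less precise than baseline-adjusted ANCOVA, and a normality check decides whether means or ranks are compared

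*Protocol article*

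**What the plan says.** The Statistics section of the protocol article sets one procedure for MEP, RRP, reaction time, gait parameters, dual-task cost and fatty acid levels.

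- A distribution check comes first: "Data will be tested for normal distribution using Shapiro-Wilk test and Q-Q-plots".
- The check selects the test: "A 2 × 2-ANOVA will be used with normally distributed data, the non-parametric equivalent for data not fulfilling assumptions of normal distribution".
- The purpose of the test is to "compare the two interventions over time (from pre- to post-measurement) on changes on the main dependent variables MEP, RRP" and the other listed variables.
- Significance testing is accompanied by one effect size for all analyses: "effect size calculation (*r* = Z/√N) will be performed".

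The stated model has the factors group and time; the baseline value is not a covariate. The Outcomes and Stepwise procedure sections have the outcomes measured before and after the intervention, so a baseline value will be available. Under Blinding, randomization, and allocation, the list is in blocks of ten, with women taking numbers 001–030 and men 031–060, so allocation is in effect stratified by sex.

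The hypothesis has no direction (Introduction: "We hypothesize that the combination will differently affect these parameters"), so a two-sided test is taken as the base case below.

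**The concern.** Three features of the stated procedure are open to question.

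1. **Precision.** A change score subtracts the whole baseline value, whatever the correlation between the two measurements. ANCOVA subtracts only the share that the data support. In a trial of 30 per arm, with fewer expected to finish, this difference can matter for the primary outcomes.
2. **Estimand.** If the check decides between a mean-based and a rank-based comparison, the quantity reported is not fixed before the data are seen. It may differ between MEP and RRP, or between a primary and a secondary outcome.
3. **Effect size.** r = Z/√N needs the Z of a rank test. An ANOVA gives F, so the default branch is paired with an effect size it does not directly produce. In either branch r is not in the units of the outcome.

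**Working it through.** **Inputs.** The Sample size section gives 27.70 (SD 5.2) and 31.49 (SD 8.6), alpha 0.05 and 80% power.

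- Difference: 31.49 − 27.70 = 3.79.
- Pooled SD: √[(5.2² + 8.6²)/2] = 7.106.
- d = 3.79/7.106 = 0.533.

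Three things are assumed: that this d is the between-arm difference at the end of the trial, that pre and post SDs are equal, and that ρ lies between 0.3 and 0.8. The article gives no ρ.

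**The plan's own figure.** The section says that "an estimated sample size of 24 participants would result in 80% power at an alpha-level of 0.05 for this parameter", without saying whether this is per arm or in total. A two-sided two-sample calculation on these inputs gives 56 per arm (normal approximation). With 24 per arm the power is 44% by noncentral t. So 24 is not reproduced; that is a separate matter on which this point does not depend. Here 24 per arm serves only as a plausible number of completers and 30 per arm as full enrolment.

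**Change score versus ANCOVA.** With two groups and two times, the interaction F is the square of the t-test on change. Per-person SDs are:

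- change score: SD × √[2(1−ρ)]
- ANCOVA: SD × √(1−ρ²)
- variance ratio, ANCOVA to change: (1−ρ²)/[2(1−ρ)] = (1+ρ)/2, below 1 for every ρ < 1.

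Power uses the noncentral t with noncentrality (d/k)√(n/2), where k is the multiplier of SD above. Example at ρ = 0.5, n = 24 per arm:

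- Change: k = 1, noncentrality 0.533 × √12 = 1.85, power 44%.
- ANCOVA: k = 0.866, noncentrality 0.616 × √12 = 2.13, power 55%.

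| ρ (assumed) | Variance ratio | 24 per arm: ANCOVA vs change | 30 per arm: ANCOVA vs change |
|---|---|---|---|
| 0.3 | 0.65 | 47% vs 33% | 57% vs 40% |
| 0.5 | 0.75 | 55% vs 44% | 65% vs 53% |
| 0.7 | 0.85 | 72% vs 65% | 81% vs 75% |
| 0.8 | 0.90 | 85% vs 82% | 92% vs 89% |

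Put as sample size, 24 per arm under ANCOVA are worth 24/0.75 = 32 per arm under the change score at ρ = 0.5, and 24/0.90 = 27 at ρ = 0.8. Below ρ = 0.5 the change score is noisier than the post value alone, because √[2(1−ρ)] exceeds 1. No gain from adding sex is counted.

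**The switch.** The article gives no cut-off, so a mechanical rule was assumed: Shapiro-Wilk at 5% in each of the four arm-by-time cells, and Mann-Whitney on change if any cell fails. Simulation used 3,000 trials per setting.

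- With truly normal data the switch fired in about 18–20% of trials, close to 1 − 0.95⁴ = 18.5%. With lognormal data it always fired.
- Type I error of the switched procedure was 0.042–0.053.
- Normal data, 30 per arm: power of switched procedure vs ANCOVA was 53% vs 64% (ρ = 0.5) and 75% vs 82% (ρ = 0.7).
- Lognormal data left untransformed, 30 per arm: Mann-Whitney on change beat ANCOVA, 49% vs 43% (ρ = 0.5) and 71% vs 55% (ρ = 0.7). ANCOVA on the log scale gave 64% and 80%.

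**The case against.** The best defence is that the planned test is valid. Under randomisation the interaction term targets the arm difference just as ANCOVA does, so the choice is one of efficiency, and the gain depends on a ρ that the article does not give. At ρ = 0.8 it is only a few points of power. ANCOVA is also not uniformly better: on strongly skewed raw data the rank test had more power. All of this stands. It limits the point to precision and makes a planned transformation part of the fix.

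A condensed article may also leave to a fuller plan the name of the rank test, the object of the normality check and the reporting of intervals. That stands too, and none of these is counted here. The choice of ANOVA and the use of a normality check to select the test are stated in the article itself.

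Three stronger readings are tempting but not supported.

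- A reader might infer that no rank equivalent of the arm-by-time contrast exists. With two times, Mann-Whitney on change scores is a direct counterpart, and the effect size r = Z/√N is compatible with it.
- A reader might infer that the fallback means separate within-arm tests whose p-values are then compared. The text describes comparing the two interventions on changes, which is a between-arm comparison.
- A reader might infer that the ANOVA branch has no possible effect size. An r-type measure can be derived from F or t. The fault is a mismatch of formula and test.

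**Conclusion.** The point holds as a matter of precision and pre-specification, not validity. The stated ANOVA answers the right question with more variance than necessary: 35% of the change-score variance is avoidable at ρ = 0.3, 25% at 0.5, 15% at 0.7 and 10% at 0.8. At 24 per arm and d = 0.53 that is a gain of roughly 14, 11, 7 and 4 percentage points of power. The direction holds for any ρ below 1 given equal pre and post SDs. The size rests on the assumed ρ and on reading the Sample size figures as a between-arm difference.

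The switch adds a second, smaller cost: whether means or ranks are compared depends on the data. It should not be described as inflating false positives, since none was seen in the settings simulated. The effect-size formula fits the rank branch only.

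**What to change.** - For each outcome, fit the post value on arm, baseline value and sex. Report the adjusted mean difference with a 95% confidence interval. Sex belongs in the model because the randomisation list is split by it.
- Drop the normality check as a gate. Fix in advance a log transformation for skewed positive outcomes such as MEP amplitude and reaction time, applied to baseline and post values alike, with the effect reported as a ratio. Outcomes that can be negative, such as dual-task cost, stay on their own scale.
- Inspect residuals. If they are poor, use bootstrap or robust intervals for the same estimand.
- Name one rank sensitivity analysis, Mann-Whitney on change scores or rank ANCOVA, and report r = Z/√N only there.

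The cost is analysis wording: the pre and post measurements are already planned, and no visit or participant is added. ANCOVA with sex uses two more degrees of freedom than the change-score test. The one real downside is that, on strongly skewed data left untransformed, ANCOVA can have less power than the rank test, so the transformations need to be settled before unblinding.

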## Abstract

A common problem in the older population is the risk of falling and related injury, immobility, and reduced survival. Age-related neuronal changes, e.g., decline in gray-and white-matter, affect neuronal, cognitive, and motor functioning. The improvement of these factors might decrease fall events in elderly. Studies showed that administration of video game-based physical exercise, a so-called exergame, or omega-3 fatty acid (FA) may improve motor and/or cognitive functioning through neuronal changes in the brain of older adults. The aim of this study is to assess the effects of a combination of exergame training with omega-3 FA supplementation on the elderly brain. We hypothesize that an intervention using a combination approach differently affects on the neuronal structure and function of the elderly's brain as compared to the sole administration of exergame training. The study is a parallel, double-blinded, randomized controlled trial lasting 26 weeks. Sixty autonomous living, non-smoking, and right-handed healthy older (>65 years) adults who live independently or in a senior residency are included, randomized, and allocated to one of two study groups. The experimental group receives a daily amount of 13.5 ml fish oil (including 2.9 g of omega-3 FA), whereas the control group receives a daily amount of 13.5 ml olive oil for 26 weeks. After 16 weeks, both groups start with an exergame training program three times per week. Measurements are performed on three time-points by treatment blinded investigators: pre-intervention measurements, blood sample after 16 week, and post-intervention measurements. The main outcomes are motor evoked potentials of the right M. tibialis anterior (transcranial magnetic stimulation) and response-related potentials (electroencephalography) during a cognitive test. For secondary outcomes, reaction time during cognitive tests and spatio-temporal parameters during gait performance are measured. Statistics will include effect sizes and a 2 × 2-ANOVA with normally distributed data or the non-parametric equivalent for data not fulfilling normal distribution. The randomized controlled study is the first to investigate the effectiveness of exergame training combined with omega-3 FA in counteracting age- and behavioral-dependent neuronal changes in the brain. This study has been registered in the Swiss National Clinical Trials (SNCTP000001623) and the ISRCTN (ISRCTN12084831) Portals.

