In the first step, the participants are handed a bathing cap that fits tightly on the head. On the top of the cap, a grid is drawn using the vertex as initial position. The vertex is determined as half distance from nasion to inion and half distance from right to left pre-tragus. As previously suggested, the optimal activation of the TA is obtained if the coil is placed parallel to and approximately 0.5–1.0 cm lateral to the midline and its mid-point is aligned anterior-posteriorly against the vertex (Cz) (Devanne et al., 1997). To maintain consistent coil positioning across sessions, detailed distance recordings are made from the nasion, inion, and bilateral pre-tragus to the vertex. In the second step, the optimal stimulation point is assessed (hotspot). The hotspot corresponds, on the grid, to the lowest motor threshold that evokes a motor evoked potential (MEP) response (Rossini et al., 1994). The third step involves determination of the resting motor threshold (RMT) defined as the lowest intensity of magnetic stimulation required to evoke MEPs of 50 μV in peak-to-peak amplitude in at least 6 of 10 consecutive trials (Rossini et al., 1994). In the fourth step, a recruitment curve (RC) of increasing intensities of 10% steps is obtained in 10 trials per step. The stimuli intensities from 90% RMT to 140% RMT are applied in a random order. The interval between the stimuli is 7 s with a 20% variance to avoid familiarization. The analysis of peak-to-peak amplitude (MEP) and RC will be performed in Matlab™ for Windows (Mathworks Inc., Natick, MA, USA).

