#### Electroencephalography

For electroencephalography (EEG) measurement, the participants wear a 20-channel dry-electrodes Enobio device (Neuroelectrics, Barcelona, Spain; Ruffini et al., 2006, 2007). The EEG system records and visualizes 24 bit EEG data at 500 Hz. The device sends the data via wireless connections to a personal computer where data can be monitored in real-time. During the EEG recording, the participants perform a Go/No-Go task including the suppression of a response in the presence of irrelevant stimuli. The stimuli presentation of the Go/No-Go task stems from the Test for Attentional Performance (TAP). The task is presented on a personal computer screen in front of the participants for about 10 min (five times 2 min). On a keyboard, the participants have to push a predefined button when the relevant stimuli appear. One investigator records the right and wrong event-related responses of the participants comparing the stimuli of the Go/No-Go task and the trigger appearing on the EEG screen. At the time point of clicking, a trigger is recorded and integrated into the EEG data recording. The trigger time points will be used for further analysis of the EEG data including response-related potentials (RRP). The analysis will be performed in Matlab™ for Windows (Mathworks Inc., Natick, MA, USA).

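### The Statistics section puts primary and secondary outcomes under one label at an unadjusted 0.05 and does not say whether one or both primaries must succeed; if either suffices, the error rate for the two primaries is about 8 to 10%

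*Protocol article*

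**What the plan says.** The Abstract states: "The main outcomes are motor evoked potentials of the right M. tibialis anterior (transcranial magnetic stimulation) and response-related potentials (electroencephalography) during a cognitive test". It continues: "For secondary outcomes, reaction time during cognitive tests and spatio-temporal parameters during gait performance are measured". Table 2 agrees. MEP and RRP are its only primary rows. Reaction time, gait parameters, dual-task cost (DTC) and fatty acid (FA) levels are secondary, and short FES-I, MMSE and GDS are listed as other.

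The Statistics section says that the groups will be compared over time "on changes on the main dependent variables MEP, RRP, RT of cognitive tasks, spatio-temporal gait parameters, DTC, and FA levels". One threshold is given for everything: a probability below "0.05 will be considered to be statistically significant".

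The Introduction sets two main objectives, one on excitability and one on neuronal activity, and ends: "We hypothesize that the combination will differently affect these parameters". It does not say whether the hypothesis is supported by a result on one parameter or only by results on both.

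For MEP, the section on transcranial magnetic stimulation says: "The analysis of peak-to-peak amplitude (MEP) and RC will be performed". It does not say which of the two is the primary quantity.

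**The concern.** The word main covers two outcomes in the Abstract and six in the Statistics section. That section fixes how significance will be judged, and it makes no distinction between the outcomes that carry the trial's claim and those that support it. Two primaries judged separately at 0.05, with no decision rule joining them, do not give a 5% error rate for the trial's single question, which is whether the combination acts differently from exergame training alone. A report could claim support from whichever primary came out positive, or present a secondary finding as a main one, and still follow the Statistics section as written.

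**Working it through.** **Inputs**
- Level per test: 0.05 (Statistics). Sidedness is not stated. I take it as two-sided because the hypothesis has no direction.
- Number of primaries: 2 (Abstract, Table 2).
- Outcomes called main in the Statistics section: 6.
- Correlation between the test statistics: not given. I show 0, 0.5 and 0.8.
- One group-by-time test per outcome is assumed.

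The article gives no family-wise figure to reproduce. Its only stated error rate is 0.05, which is correct for a single test.

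**Outcome status, side by side**

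| Outcome | Table 2 | Statistics |
|---|---|---|
| MEP | primary | main |
| RRP | primary | main |
| Reaction time | secondary | main |
| Gait parameters | secondary | main |
| DTC | secondary | main |
| FA levels | secondary | main |

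**Two primaries, success if either is significant, no true effect on either**
- Independent: 1 − (1 − 0.05)² = 1 − 0.9025 = 0.0975.
- Correlated: simulated pairs of two-sided z-tests (400,000 draws, limit 1.96) give 9.1% at correlation 0.5 and 7.9% at 0.8.

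**Two primaries, success only if both are significant**
- No true effect on either, independent: 0.05² = 0.0025.
- A real effect on one only: at most 0.05. There is no inflation.

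**Illustration only: all six count, one test each, no true effect on any**
- Independent: 1 − 0.95⁶ = 0.265.
- Without FA levels: 1 − 0.95⁵ = 0.226.
- Six tests, correlated (simulated): 20.8% at 0.5, 13.8% at 0.8.

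**Effect of splitting the level over the primaries**
- At 0.025 each, independent: 1 − 0.975² = 0.0494. Under any correlation it is at most 0.05. Holm gives the same protection with more power.

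**Power cost (normal approximation, assuming 24 per arm)**
- The effect with 80% power at two-sided 0.05 is d = (1.960 + 0.842) × √(2/24) = 0.81. This value is hypothetical and is not in the article.
- Its power at 0.025 is Φ(2.802 − 2.241) = Φ(0.560) = 0.71. Keeping 80% would need 30 per arm.
- The Sample size section's own figures give a difference of 31.49 − 27.70 = 3.79, a pooled SD of √((5.2² + 8.6²)/2) = 7.11, and d = 0.533. Then d/√(2/24) = 1.847. Power is Φ(1.847 − 1.960) = 0.46 at 0.05 and Φ(1.847 − 2.241) = 0.35 at 0.025.

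**The case against.** The strongest reply is that the label main is loose wording and nothing more. The six variables in the Statistics section are exactly the primary and secondary rows of Table 2, and the ones left out are exactly its other rows. The section never calls the six primary, and Table 2 already holds a clear hierarchy. It can also be said that the two primaries answer two separate objectives, where adjustment is debated, and that a full protocol or analysis plan may contain an adjustment.

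Much of this stands. Table 2's hierarchy is clear, so the correction is to wording. The lack of an adjustment in a condensed article would not by itself be a finding. What remains is in the text shown: a label that conflicts with the Abstract and Table 2, and a flat threshold alongside a hypothesis that covers both parameters without a decision rule.

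A reader might infer more, and the article does not support it:
- **That any single p < 0.05 counts as success.** This is one reading of an unstated rule. The inflation depends on it.
- **That the true error rate is 26.5%.** That figure counts four outcomes that Table 2 lists as secondary and assumes six independent true nulls. FA levels mark intake of the supplement and are expected to differ between fish oil and olive oil.
- **That MEP will be tested separately at six intensities.** No such tests are planned. The steps from 90% to 140% of resting motor threshold serve to build a recruitment curve.
- **That RRP is open to free choice over 20 channels.** The component, electrode and time window are details that an article may leave to the full protocol.

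**Conclusion.** The point holds in limited form. The Statistics section conflicts with the Abstract and Table 2 on which outcomes are main, and it judges both primaries at an unadjusted 0.05 with no rule for combining them. If a positive result on either primary supports the hypothesis, the family-wise type I error for the two is 9.75% under independence, and about 9.1% and 7.9% at correlations of 0.5 and 0.8. It would be higher if the other variables labelled main also counted, by an amount the article does not let one fix. These figures assume one test per primary and no true effect on either. If both primaries must be significant, the inflation disappears, so stating the rule is itself a remedy.

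**What to change.** 1. In the Statistics section, replace the six-variable list under the label main with the primary outcomes (MEP, RRP) and the secondary outcomes (reaction time, gait, DTC, FA levels), as in Table 2.
2. State the rule for the primaries. Either use Holm at an overall two-sided 0.05 (the smaller p-value against 0.025 and, if that is significant, the larger against 0.05), or require both to be significant at 0.05.
3. Report the four secondary outcomes with estimates and 95% confidence intervals, and make no confirmatory claim from them.
4. Before unblinding, name one summary for each primary. For MEP this could be a single recruitment-curve summary, such as the area under the curve from 90% to 140% of resting motor threshold. It is best done before any by-group analysis, because groups coded A and B can still be compared by p-value.

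**Cost.** No visit, measurement or enrolment changes. Under Holm, the hypothetical effect with 80% power at 24 per arm has about 71% on the first step. Under the both-required rule, two such effects with independent estimates would have 0.80 × 0.80 = 64%. With the article's own means and SDs, power at 24 per arm is already only about 45% at 0.05 and falls to about 35% at 0.025. That is a separate sample-size issue and should be handled as such.
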